### Data analysis

Qualitative variables will be presented as proportions, while for quantitative variables, the mean (standard deviation) or median (interquartile range), after checking for normality using the Shapiro-Wilk test, will be used. To compare variables across groups, Student *t* tests or Mann-Whitney *U* tests for continuous data and chi-square tests or exact tests for categorical variables will be carried out. Before parametric hypothesis testing, equality of variances will be studied using the Levene’s test, and if assumptions are not met, contrasts will be performed with the Welch’s test. An intention-to-treat approach will be followed. Two-tailed *P* values will be presented and a significance level of 0.05 will be used.

For the secondary outcomes, adjustment with the Benjamini-Hochberg procedure will be carried out.

A sub-analysis of the effect of treatment on compliers will be performed for the main outcome. Compliers are defined as those subjects that effectively receive the treatment they are allocated to. For the present study, compliers will be defined as individuals that, having been randomized to the intervention, complete at least two out of three medical visits and at least five out of seven psychological interventions. For the statistical analysis, instrumental variable analysis will be carried out. A two-sided probability (*p*) value of less than 0.05 will be considered to indicate statistical significance. The statistical analysis was performed using R (https://www.rstudio.com/) statistical software.

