#### General procedures

The study subjects will be assigned to one of two arms, and the intervention program will be compared to the standard-of-care clinical practice. The baseline visit will take place 4 to 6 weeks after hospital discharge, and two follow-up visits will take place 3 and 6 months after.

The intervention program will consist of an early care therapeutic education on prevention and management of PICS and chronic pain during the three scheduled medical visits within the first 6 months after hospital discharge and psychological treatment for patients at risk of emotional distress.

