#### Baseline visit

The baseline visit will take place between 4 to 6 weeks after hospital discharge. Information regarding the study will be given to the patient, and informed consent will be obtained. After that, the patient will be randomized. During this first visit, demographic data, medical history, and ICU and hospitalization variables will be collected from all the included patients, regardless of their randomization arm. All patients will complete a series of questionnaires to evaluate their quality of life and the presence of anxiety, depression, or post-traumatic stress disorder. The presence of pain and its influence on the patients’ lifes will also be evaluated.

Intervention group

The intervention consists of a program that includes early patient care, therapeutic education, and psychological intervention. It will be implemented across three medical visits scheduled as follows:
Visit 1 Intervention group, 4 to 6 weeks after hospital discharge.Visit 2 Intervention group, 8 weeks after hospital discharge.Visit 3 Intervention group, 18 weeks after hospital discharge.

Components:
Interview and physical examination.Therapeutic education about the PICS, orally and in writing with specific documents delivered at the end of the visit, i.e., a PICS fact-sheet developed by the investigators and a rehabilitation manual recommended by the Follow-up and Rehabilitation Committee of the Argentine Society of Intensive Care, SATI [14].Therapeutic education about pain (if the patient reports pain) which includes an explanation of pain neurophysiology, the rational use of drugs prescribed by other specialists, information about how to manage daily life activities, and the importance of pre-emptive pain management for proper rehabilitation.

A psychological intervention will be conducted if the following criterium is met: a score higher than 8 on the hospital anxiety and depression (HAD) test depression subscale (supplement, questionnaire Q1) [17]. The intervention protocol will consist of 7 weekly sessions lasting one and a half hours each (supplement, Table 1). The intervention in depression is based on Rehm’s model of self-control. Psychological interventions may cause adverse events resulting in worsening of patients’ clinical course (overdose, self-harm, and self-harm attempts). Therefore, the investigators will monitor any related symptom, report it as an adverse event, and refer the patient for treatment by a specialist unit.

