The impact of the intervention program on the incidence of anxiety or depression will be assessed by the Hospital Anxiety and Depression test (HAD) (supplement, questionnaire Q1) [17], consisting of 14 questions, with two subscales, one for anxiety and the other for depression, with seven items each and a maximum score of 21 for each subscale. The cut-off points are as follows: 0 to 7 imply the absence of clinically relevant anxiety and depression, 8 to 10 imply de presence of symptoms that require consideration, and 11 to 21 it report the presence of relevant symptoms, with a very probable diagnosis of anxiety or depression. According to Bjelland’s review, cut-off points equal or greater that 8 will be used as abnormal anxiety or depression’s values. This test will be performed at the baseline visit and at 3 and 6 months [25].

Finally, the incidence of post-traumatic stress disorder (PTSD) [26] will be evaluated with the post-traumatic stress disorder checklist questionnaire (PCL-5) [27]. It contains 20 questions that correspond to the DSM-V criteria. Participants will rate their symptoms on a scale of 0 (not at all), 1 (slightly), 2 (moderately), 3 (quite) to 4 (extremely), with a score ranging from 0 to 80. The overall severity of the symptoms can be assessed adding up the scores of each question (interval 0–80). The severity of each symptom can also be evaluated adding up the scores of the questions. DSM-5 symptom cluster severity scores can be obtained by adding up the scores for the items within a given cluster, i.e., cluster B (items 1–5), cluster C (items 6–7), cluster D (items 8–14), and cluster E (items 15–20). A provisional PTSD diagnosis can be made by treating each item rated 2 (“moderately”) or higher as a symptom endorsed, then following the DSM-5 diagnostic rule which requires at least: 1 B item (questions 1–5), 1 C item (questions 6–7), 2 D items (questions 8–14), and 2 E items (questions 15–20) (supplement, questionnaire Q6).

For this analysis, questionnaire licensing was obtained. The validated version in Spanish was used for each of them, except for PCL-5 which, being a new questionnaire, is not yet validated in Spanish, but it has the advantage of screening PTSD according to the DSM-V criteria. The questionnaires are shown in the supplement.

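### The complier rule counts psychological sessions that are offered only to patients above a HAD depression cut-off, so patients who receive everything offered are non-compliers and the complier effect is biased whenever education alone works

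*Protocol article*

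**What the plan says.** All from the protocol article.

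- **Data analysis, general definition:** "Compliers are defined as those subjects that effectively receive the treatment they are allocated to".
- **Data analysis, operational rule (next sentence):** patients randomized to the intervention are compliers if they "complete at least two out of three medical visits and at least five out of seven psychological interventions". No exception is made for patients who are not offered sessions. The method is instrumental-variable analysis, as a sub-analysis of the main outcome. The general approach is intention to treat.
- **General procedures:** the program is education at three medical visits plus "psychological treatment for patients at risk of emotional distress".
- **Baseline visit, intervention group:** "A psychological intervention will be conducted if the following criterium is met", namely "a score higher than 8 on the hospital anxiety and depression (HAD) test depression subscale". For those patients, "The intervention protocol will consist of 7 weekly sessions lasting one and a half hours each".
- **Control group:** follow-up is by referring physicians outside the study, so controls are not offered the program.
- **Outcome measurements:** for classifying outcomes, "cut-off points equal or greater that 8 will be used as abnormal anxiety or" depression values.

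**The concern.** The two definitions of a complier disagree for an identifiable group: intervention patients at or below the HAD depression trigger. They can attend all three visits, and so meet the general definition, yet they cannot reach five sessions because none are offered to them.

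This matters because of the estimator. Instrumental-variable analysis with randomization as the instrument attributes the whole between-arm difference to the compliers. That is valid only if assignment does nothing to the outcome of non-compliers. Here the non-compliers include everyone given education visits without sessions, and the article presents education as an active part of the program. Any benefit they gain is moved onto a smaller group. At stake is whether the complier effect reported for the primary outcome means what it is said to mean, and whether it is exaggerated.

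**Working it through.** **Figures in the plan.** The article gives no complier share, no share above the HAD cut-off and no expected complier effect, so there is no complier figure to reproduce. The Sample size section gives a control mean of 50 EQ-VAS points and a relevant difference of 20%, read here as 0.20 × 50 = 10 points. It also gives 51 patients per arm. The 10 points only set a scale; the ratios below do not depend on it.

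**Estimator.** Wald estimate = ITT difference ÷ (complier share, intervention arm − complier share, control arm). The control share is 0 because controls are not offered the program.

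**Step 1: ceiling on the complier share.** Let s be the share of the intervention arm above the trigger (an assumption, shown over a range). As written, the complier share cannot exceed s. With full attendance it equals s, and the ITT effect is multiplied by 1/s.

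**Step 2: worst case.** Suppose the true effect is 10 points in everyone who receives what they are offered, with or without sessions. The last column assumes that 80% of those offered sessions complete at least five, and that the others gain nothing. Then ITT = 10 × (1 − 0.2s) and the complier share is 0.8s.

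| s | Possible compliers of 51 | 1/s | Wald, full attendance | Wald, 80% complete sessions |
|---|---|---|---|---|
| 0.2 | 10.2 | 5.0 | 10/0.2 = 50 | 9.6/0.16 = 60 |
| 0.3 | 15.3 | 3.3 | 10/0.3 = 33.3 | 9.4/0.24 = 39.2 |
| 0.5 | 25.5 | 2.0 | 10/0.5 = 20 | 9.0/0.40 = 22.5 |
| 0.7 | 35.7 | 1.4 | 10/0.7 = 14.3 | 8.6/0.56 = 15.4 |

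If compliance is judged against what was offered, the complier share is 1 − 0.2s (0.96 to 0.86 over this range), or 1 with full attendance. The Wald estimate is then 10 in every row, which is the true value.

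**Step 3: how much of the multiplier is bias.** A complier effect should exceed the ITT effect when few comply, so 1/s is not itself an error. Let education add e points in every intervention patient and sessions add p more in those offered them, with e + p = 10 and full attendance.

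- ITT = e + p·s
- Wald as written = e/s + p
- True effect in compliers = e + p
- Bias = e(1/s − 1)

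| Wald ÷ true complier effect | s = 0.2 | s = 0.3 | s = 0.5 | s = 0.7 |
|---|---|---|---|---|
| e = 0, p = 10 | 1.00 | 1.00 | 1.00 | 1.00 |
| e = 2, p = 8 | 1.80 | 1.47 | 1.20 | 1.09 |
| e = 5, p = 5 | 3.00 | 2.17 | 1.50 | 1.21 |
| e = 10, p = 0 | 5.00 | 3.33 | 2.00 | 1.43 |

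Example, s = 0.3 and e = p = 5: ITT = 5 + 5 × 0.3 = 6.5; Wald = 6.5/0.3 = 21.67; true = 10; ratio 2.17. The bias disappears only if education without sessions does nothing, or if everyone is above the trigger.

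**The case against.** The strongest reply is that the general definition already supplies the sensible reading: a patient without an indication for sessions was not allocated them, and a fuller plan may say so. This does not hold against the text. The operational sentence states an explicit joint requirement, and the abstract says that the article sets out the statistical analysis plan. The rule is stated, not left open. Reading it as a deliberate full-dose definition does not help either, because the exclusion restriction still fails.

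Several limits do stand, and a reader might infer more than the article supports:

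- *Most of the intervention arm can never comply.* This needs s below 0.5. The article gives no share, and the inclusion criteria point to a severely ill ICU population in which s could be high.
- *The effect is grossly inflated.* The ratio to the true complier effect runs from 1.0 to 5.0 over the range above, depending on s and on the education effect. Neither is known.
- *The instrument is weak.* With about 41 analyzed per arm (51 × 0.8) and no control compliers, the first-stage F is about 40c/(1 − c) for complier share c. At c = 0.32 it is 40 × 0.32/0.68 = 18.8; at c = 0.18 it is 40 × 0.18/0.82 = 8.8. Strength turns on the same unstated share.
- *The trial's main conclusion is compromised.* It is not. The intention-to-treat analysis, the sample size and the secondary outcomes do not use the complier rule.
- *The two HAD cut-offs directly contradict each other.* One triggers sessions and the other classifies outcomes, so they serve different purposes. A score of exactly 8 is abnormal as an outcome but does not trigger sessions. Only the trigger decides who can be a complier.

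**Conclusion.** The complier rule is wrong as written. It makes non-compliers of patients who received everything they were offered, contradicts the general definition beside it, and breaks the exclusion restriction on which the planned instrumental-variable analysis rests. If education helps patients who get no sessions, the complier effect on the primary outcome is biased away from zero by e(1/s − 1) points under full attendance. This assumes that education and sessions act in the same direction and that controls get none of the program. The size cannot be fixed from the article, because neither s nor e is given. The defect is confined to this one sub-analysis.

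**What to change.** Replace the operational sentence with a rule relative to what each patient was offered: at least two of three medical visits for all intervention patients and, only for those for whom sessions were indicated under the criterion in the Baseline visit section, at least five of seven sessions.

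Also:

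- State the remaining assumption that exposure below these thresholds has no effect. Optionally add a sensitivity analysis with a lower threshold. Counting any single visit may come close to intention to treat, because the first intervention visit falls in the same 4-to-6-week window as the baseline visit.
- Say which HAD assessment determines the indication, since HAD is repeated at 3 and 6 months.
- Make clear that the session criterion in the Baseline visit section, not the outcome cut-off in Outcome measurements, governs the complier rule as written, or reconcile the two passages.

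The cost is a reworded sentence, these short clarifications and at most one extra run, with no new data. The change should be dated before outcomes by arm are seen, since a complier rule altered afterwards would look data-driven.

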### Dissemination policy

Investigators will communicate the trial results to participants, healthcare professionals, and the general public by posting them in results databases. The purpose of the data collection is specific to achieving the objectives defined in the project. The data collected during the study will be included in the investigators file master owned by the center.

The treatment and communication of personal data of all participants will be in compliance with the Regulation EU 2016/679 of the European Parliament and of the Council of April 27, 2016, on the protection of natural persons as regards the treatment of personal data and the free circulation of data, effective as of May 25, 2018, and to Organic Law 3/2018, of December 5, on the Protection of Personal Data and guarantee of digital rights.

## Discussion

As far as we know, this is the first randomized clinical trial that examines the effectiveness of an early care therapeutic education and psychological intervention for the management of post-intensive care syndrome and chronic pain after COVID-19.

Patients who survive a critical illness often experience disturbances in many areas, with pain being one of the most important topics. Unfortunately, lack of adequate care to manage this pain is often a problem during the patients stay in the units [5]. This study would quantify the impairment on quality life after ICU admission, as well as the incidence of chronic pain, anxiety, depression, and PTSD. The health status derived from our analysis could be used in economic evaluations of healthcare systems and long-term impact and consequences of the pandemic. Likewise, if the effectiveness of our intervention is verified, it would serve as proof of the need to implement early care programs that allow the recovery process to be followed from early stages, given the current scenario of the pandemic.

Being an integral part of this syndrome, and in order to avoid the limitations and effects of pain on the patient’s quality of life, pain management should be introduced in the ICU.

This project has some limitations.

The main one is that patients meeting inclusion criteria (especially those who have had a more severe course of the disease) may have a severe mobility limitations that would prevent them from attending some trial visits, which would result in a selection bias. This would add to the problem of a small population sample as a consequence of the study being carried out in a single center.

In addition, there are risk factors associated with the development of PICS and chronic pain after a critical illness. These include older age, low socioeconomic status, female gender, previous mental health problems, negative ICU experiences, and delirium.

Therefore, an exploratory analysis of risk factors potentially associated with PICS due to COVID-19 will be carried out, although the sample size will be a determining factor in the conclusions

Future development of multi-center projects may overcome this limitation.

Finally, since this intervention program involves face-to-face visits, the pandemic could limit its correct development.

Restrictions on mobility might make hospital follow-up visits difficult.

## Trial status

Protocol version number 1.0 (April 29, 2020)

Recruitment status: recruiting ongoing (started: May 27, 2020). Recruitment is anticipated to be completed by September 25, 2020, and study completion by March 25, 2021.

## Abbreviations

PICS: Post-intensive care syndrome
ICU: Intensive care unit
HRQoL: Health-related quality of life
ARDS: Acute respiratory distress syndrome
ICU-AW: Intensive care unit-acquired weakness
MMSE: Mini-mental state exam
VAS: Visual analog scale
EQoL 5D/5 L: European quality of life 5 dimensions/5 levels
BPI: Brief Pain Inventory
HAD: Hospital Anxiety and Depression HAD Scale
